##### Sham acupuncture group (SA)

Non-penetrating acupuncture at non-acupoints will be performed using the Park sham acupuncture device (0.25 mm in diameter and 40 mm in length, Hwatuo, Suzhou, China) for participants in the SA group. Corresponding to the verum acupuncture group, two sets of non-acupoints will be applied alternately. The first set of sham acupoints includes bilateral non-acupoint 1, bilateral non-acupoint 2, non-acupoint 3, non-acupoint 4, bilateral non-acupoint 5, and bilateral non-acupoint 6. The second set consists of bilateral non-acupoint 7, bilateral non-acupoint 8, bilateral non-acupoint 9, and bilateral non-acupoint 10. The locations of the sham acupoints are shown in Table 2 and Figures 2, 3 illustrates the Park sham acupuncture device.

**Table 2 tab2:** Locations of non-acupoints used in the sham acupuncture group.

Non-acupoints	Locations
Non-acupoint 1	On the central area of the tibia, 6 cun above the tip of the lateral malleolus.
Non-acupoint 2	On the outer side of the upper arm, 4 cun above the elbow crease, at the midpoint between the large intestine meridian and lung meridian.
Non-acupoint 3	On the lower abdominal area, the left side of Qihai (CV6), at the midpoint between the stomach meridian and spleen meridian.
Non-acupoint 4	On the lower abdominal area, 6 cun lateral to Guanyuan (CV4) on the right side.
Non-acupoint 5	On the outer side of the forearm, 6 cun above the wrist crease, between the large intestine meridian and sanjiao meridian.
Non-acupoint 6	On the thigh area, 4 cun above the patellar base, at the midpoint between the stomach meridian and gallbladder meridian.
Non-acupoint 7	On the back, 3 cun lateral to Ganshu (BL18).
Non-acupoint 8	On the back, 3 cun lateral to Pishu(BL20).
Non-acupoint 9	On the back, 3 cun lateral to Shenshu(BL23)
Non-acupoint 10	On the inner side of the lower leg, 8 cun above the tip of the medial malleolus, at the midpoint between the kidney meridian and spleen meridian.

**Figure 2 fig2:**
[figure not shown]
Locations of non-acupoints.

**Figure 3 fig3:**
[figure not shown]
Park sham acupuncture device.

During treatment, participants will lie in a supine or prone position, and the Park device will be attached to the skin over the sham acupoints through the ring base. The blunt and retractable needle will be inserted into the plastic tube, and the needle will retract into the handle when the blunt tip contacts the skin. Thus, there will be no Deqi sensation.

##### Waitlist control group

Participants assigned to the waitlist control group will be instructed not to receive any therapy during the 8-week waiting period, but regular health follow-up through telephone will be conducted once a week by an appointed investigator. Furthermore, participants will be able to report their feelings to the investigator at any time. For those whose symptoms worsen during the waiting period, specialists at the Affiliated Hospital of Chengdu University of Traditional Chinese Medicine will be contacted immediately for symptomatic treatment, and intensive symptom monitoring will be implemented until symptoms return to their previous level. For participants whose exacerbated symptoms show no significant improvement or who develop new illnesses, withdrawal from the study will be recommended, and they will be advised to seek appropriate treatment. Participants who complete the 8-week waiting period will receive the same acupuncture treatment as the VA group for free.

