#### Randomization and blinding

An appointed investigator who is not involved in participant recruitment, treatment, outcome assessment, or data analysis will generate the random sequence using SAS version 9.4 (SAS Institute, Inc) through a simple randomization method. The acupuncturist, who will not be involved in participant recruitment, will receive the grouping information for each participant from this investigator via short message service (SMS).

Participants in the VA and SA groups will be blinded to treatment allocation. VA and SA treatments will be performed in separate treatment rooms to reduce the risk of accidental unblinding. Participant recruitment, outcome assessment, imaging processing, and data collection, management, and analysis will be performed by independent investigators. The VA, SA, and waitlist control groups will be coded as A, B, and C, respectively, throughout the trial period until the completion of the primary analysis to ensure concealment of treatment assignment. It will be difficult to blind participants in the waitlist control group because they will not receive treatment immediately. A participant’s treatment allocation will be unblinded in the event of SAEs occurring during the trial.

The success of blinding will be evaluated for participants in the VA and SA groups at two time points (the first week and the 8th week after treatment) by asking them to guess their group allocation. The Bang’s blinding index (Bang’s BI) will be calculated according to the guessed proportion of each arm (52, 53).

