#### Interventions

Healthy controls (HCs) will not receive any intervention during the trial period; clinical and brain imaging data will be collected only once. All interventions will be carried out in the outpatient department of the Affiliated Hospital of Chengdu University of Traditional Chinese Medicine. A trained and certified acupuncturist with at least 5 years of working experience will administer the interventions. The treatment protocol consists of 24 sessions, each lasting 30 min, administered over 8 weeks (three sessions per week). The acupuncturist will twirl and lift or thrust needles for 10 s every 15 min during each treatment session. The acupuncturist is not allowed to discuss the effects of acupuncture with the participants during the treatment period.

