#### Physical activity monitoring

Physical activity (PA) is a major factor that triggers the exacerbation of symptoms in patients with ME/CFS. To control the influence of variation in PA on study results, accelerometer-based PA monitoring will be performed. All participants will be instructed to wear an ActiGraph wGT3X-BT accelerometer (ActiGraph LLC, Pensacola, FL, USA) on the left wrist at all times throughout the 8-week trial period, except during sleep or water-based activities such as showering and swimming. Moreover, two appointed investigators will contact participants through WeChat (a social media platform in China) video calls between 8:30 a.m. and 9:00 a.m. each day to ensure adherence. The accelerometer-collected data will be exported every 2 weeks.

ActiLife version 6.13.4(ActiGraph Corporation) will be used to download and analyze the accelerometer data. The raw data will be converted into counts of movement using 60-s epoch lengths(ct/min). Non-wear time will be defined as zero accelerometer counts for any continuous 90 min. A day will be considered valid if the wear time is ≥ 10 h. Summary measures will be calculated using the average values across all valid days, including total PA time (min/day >100 ct/min), sedentary time (min/day for ≤100 ct/min), light PA time (min/day for 100–2019 ct/min), moderate PA time (min/day for 2020–5,998 ct/min), and vigorous PA time (min/day for ≥5,999 ct/min).

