##### Adverse events and safety

Any adverse events (AEs) or serious adverse events (SAEs) occurring during the intervention, whether related to the intervention or not, will be recorded in case report forms (CRFs) in detail (including the onset pattern, onset time, duration, severity, frequency, and treatment). Investigators will assess the relationship between AEs or SAEs and acupuncture treatment according to factors such as cause, timing, and clinical course. Common AEs related to acupuncture (including fainting, stuck needles, broken needles, bent needles, bleeding, edema, and other minor AEs) will be treated by the acupuncturist immediately. For SAEs, such as stroke recurrence or organ damage, researchers will immediately stop the treatment and send the patient to the emergency department. SAEs will be reported to the ethics committee within 24 h. The research team will bear the treatment costs for all AEs and SAEs.

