#### Statistical analysis

Statistical analysis will be conducted by an appointed statistician blinded to group allocation using R software (version 4.2.1; R Foundation). Intergroup comparisons of RSFC will be performed using the DAPBI toolbox. Normally distributed continuous variables will be reported as mean±standard deviation, while non-normally distributed data will be reported as median [P25 P75]. A *p*-value of <0.05(two-tailed) will be set as the significance level for all analyses.

The intention-to-Treat (ITT) protocol will be used for the analysis of all outcomes. The ITT population will include all participants who are randomized, regardless of treatment adherence or protocol deviations. The missing value will be handled using multiple imputations.

First, intergroup comparisons of demographic data (such as age, sex, and educational level), illness duration, estimated premorbid intelligence function, and PA will be conducted to examine comparability across the three groups. Categorical data will be analyzed using the χ^2^ test. Normally distributed continuous variables will be tested using one-way analysis of variance (ANOVA), whereas the non-normally distributed data will be analyzed using the Kruskal–Wallis test.

Analysis of covariance (ANCOVA) will be applied to the primary outcome and other cognitive measures, with age, estimated premorbid intelligence ability, and PA as covariates. ANCOVA with age and PA as covariates will be used for clinical measures and brain metabolites. Repeated measures ANOVA will be used to compare differences in hippocampal functional connectivity among the three groups. Age, sex, and years of education will be included as covariates. *Post hoc* analysis will be performed for RSFC with interaction effects. Multiple comparisons for hippocampal functional connectivity will be corrected using cluster-level family-wise error (FWE) correction, with a significance threshold set at a p-value of < 0.05. The χ2 test will be used to compare the rate of AEs and SAEs between the groups. Finally, Spearman correlation analysis will be performed to examine the relationships between cognitive outcome measures and imaging indicators exhibiting intergroup differences.

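### Health follow-up is stated differently for the waitlist arm than for the acupuncture arms, so AE comparisons with waitlist may partly reflect how events are found

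*Protocol article*

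**What the plan says.** All references are to the protocol article.

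- **Waitlist control group.** For the 8-week wait, "regular health follow-up through telephone will be conducted once a week by an appointed investigator". In addition, "participants will be able to report their feelings to the investigator at any time", and if symptoms worsen, "intensive symptom monitoring will be implemented until symptoms return to their previous level". These three arrangements are stated for this arm only.
- **Interventions.** For VA and SA, "The treatment protocol consists of 24 sessions, each lasting 30 min, administered over 8 weeks (three sessions per week". No health call is stated for either arm.
- **Randomization and blinding.** The acupuncturist "will receive the grouping information for each participant from this investigator via short message service (SMS", and so is not blinded.
- **Physical activity monitoring.** Accelerometer wear covers all participants for the 8 weeks, with "video calls between 8:30 a.m. and 9:00 a.m. each day to ensure adherence". Two appointed investigators make these calls.
- **Adverse events and safety.** Any AE or SAE is to be recorded on the CRF, regardless of relatedness. Common acupuncture AEs "will be treated by the acupuncturist immediately". Investigators judge relatedness.
- **Statistical analysis.** A chi-square "test will be used to compare the rate of AEs and SAEs between the groups", at the two-tailed 0.05 level set for all analyses.

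**The concern.** A comparison of AE rates between arms is interpretable only if an event has a similar chance of coming to light in each arm. Here the stated health contact differs by arm in mode (telephone or clinic), frequency (weekly or three times a week) and person (an appointed investigator or the unblinded treating acupuncturist). One test then uses the events from all of these routes.

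Because unrelated events count too, symptom worsening and new illness belong in the AE tally. These are what a health call would be expected to pick up, and the only stated health call is on waitlist. Brief, minor events may instead surface more readily at frequent clinic visits. The two mechanisms pull in opposite directions.

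What is at stake is the safety comparison with no treatment. The article itself names physical activity as a major trigger of symptom exacerbation in ME/CFS, and the VA and SA arms make 24 clinic attendances. Exacerbation is therefore an event on which that comparison should be fair.

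**Working it through.** **Step 1. Contacts stated over 8 weeks (56 days).** The plan's own figure reproduces: 3 sessions × 8 weeks = 24.

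| Contact | VA | SA | Waitlist |
|---|---|---|---|
| Treatment sessions | 3 × 8 = 24 | 3 × 8 = 24 | 0 |
| Stated health calls | 0 | 0 | 1 × 8 = 8 |
| Any-time reporting route stated | no | no | yes |
| Closer monitoring on worsening stated | no | no | yes |
| Daily accelerometer-adherence calls | up to 56 | up to 56 | up to 56 |

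The VA and SA columns are identical. The asymmetry lies only between those two arms and waitlist. The last row is common to all arms, but its stated purpose is not AE enquiry.

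**Step 2. What unequal capture would do to the test.** The document gives neither AE risks nor capture probabilities, so both are assumptions here. I also assume the same 8-week recording window in every arm and a three-group reading of the chi-square test.

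Inputs: n = 43 per arm (Sample size calculation); α = 0.05 (Statistical analysis); the same true risk p in every arm; capture probability d in each arm.

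- Observed rate in an arm: r = p × d.
- Noncentrality: λ = n × Σ(r − r̄)² / [r̄(1 − r̄)], summed over the three arms, where r̄ is their mean.
- False rejection: the probability that a noncentral chi-square with 2 df and noncentrality λ exceeds 5.99.

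With p = 0.30:

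- *Capture 0.9 in all arms.* λ = 0, so rejection is 5%.
- *Capture 0.9 / 0.9 / 0.8 (VA / SA / waitlist).* r = 0.27, 0.27, 0.24 and r̄ = 0.26. λ = 43 × (2 × 0.01² + 0.02²) / (0.26 × 0.74) = 43 × 0.0006 / 0.1924 = 0.134. Rejection is 6.0%.
- *Capture 0.9 / 0.9 / 0.6.* r = 0.27, 0.27, 0.18 and r̄ = 0.24. λ = 43 × (2 × 0.03² + 0.06²) / (0.24 × 0.76) = 43 × 0.0054 / 0.1824 = 1.273. Rejection is 15.7%.
- *Reversed, 0.6 / 0.6 / 0.9.* r = 0.18, 0.18, 0.27 and r̄ = 0.21. λ = 43 × 0.0054 / (0.21 × 0.79) = 1.400. Rejection is 16.9%.

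Simulation with 40,000 trials per setting agrees: 4.9%, 5.8%, 15.5% and 16.7% in the same order.

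**Step 3. Sensitivity to the assumed risk.** For capture of 90% against 60%, simulated rejection is about 7% at a true risk of 10%, and about 29% to 30% at 50%. For 90% against 80% it is about 7% at a true risk of 50%.

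**The case against.** The strongest reply is that the article does not say participants in the VA and SA arms are not asked about their health. AE recording is not limited to one arm, and a journal article commonly leaves the question script and schedule to the full protocol and CRF. The weekly waitlist call can also be read as making up for the absence of clinic visits, which narrows the gap. This stands in part. The point cannot rest on a missing AE procedure, and it does not. It rests on three arrangements that the article states for one arm only. A common procedure elsewhere would not neutralise them unless the comparison were restricted to events found by it.

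Some stronger readings are tempting but not supported:

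- *That contact is 24 against 8, so a calculable share of waitlist events is lost.* Adding the adherence calls gives up to 24 + 56 = 80 against 8 + 56 = 64. A model with a 3-day recall window would have a weekly call capture 3/7 = 43% of events. If the daily calls were credited in the same way, capture would be complete in every arm. The sessions are not described as AE enquiries either, so there is no ground for crediting them and not the calls. Waitlist participants can also report at any time.
- *That only waitlist is asked about worsening.* This is inferred from silence.
- *That an unblinded acupuncturist collects the AEs.* The article says the acupuncturist treats common ones, not that the acupuncturist elicits or records them.
- *That harm in the treated arms would be hidden.* Fatigue, sleep, anxiety, depression and quality of life are measured as changes from baseline to week 8 in the trial, so sustained worsening has a common measure. Transient exacerbation between those two points does not.

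Finally, the wording of the chi-square test does not say that all three arms enter one test. The illustration depends on that reading.

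**Conclusion.** The point holds in limited form. As written, health follow-up differs between waitlist and the two acupuncture arms, and AE and SAE rates are compared between the groups without restriction to events found in a common way. Comparisons of VA or SA with waitlist may therefore partly reflect detection. The VA against SA comparison is untouched by the contact schedule, and so is the primary outcome.

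The size of the bias is not known. A modest capture gap does little harm, while a wide gap with frequent events could roughly triple the nominal 5% error rate or do worse, but every such figure rests on assumed risks and capture rates. The net direction is not known either, since it may differ by type of event. This is worth correcting before enrolment, because no analysis can recover events that were never elicited. It is not a defect that threatens the trial's main conclusion.

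**What to change.** Add one short scripted AE question set, including symptom worsening and new illness, asked once a week from randomisation to week 8 in all three arms. Ask it within the daily video calls already planned, through the same investigators and onto the same CRF page.

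In the Statistical analysis section, state that any comparison with waitlist uses events found by this common enquiry. Report events seen only at treatment sessions (for example stuck or bent needles, bleeding, fainting) separately, for VA against SA. Leave the waitlist health call and its monitoring as they are.

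The cost is protocol wording and a one-page CRF script, with no new visits or staff. The downside is a slightly longer call once a week and more minor events on record.

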#### Sample size calculation

The PASS software (version 21.0.3) was used to calculate the sample size. Based on two acupuncture trials that used the Symbol Digit Modalities Test (SDMT) as the primary outcome (56, 57), we estimated that the mean and standard deviation of the change in the SDMT score at week 8 after randomization would be 3.75 ± 4.95, 2.45 ± 5.21, and 1.30 ± 4.35 for the VA, SA, and waitlist control groups, respectively. With *α* = 0.05, *β* = 0.2, a power of 0.8, and a two-sided test for group differences, 36 participants are required in each group. Assuming a 20% dropout rate, 43 cases are needed per group, resulting in a total sample size of 129 participants.

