## Methods and analysis

### Study design

This is a prospective, three-armed randomized controlled trial using rs-fMRI and ^1^H-MRS, which will be jointly conducted by two hospitals in Chengdu. A total of 129 patients with ME/CFS occurring after COVID-19 and 30 HCs who have fully recovered from COVID-19 will be recruited. After baseline assessment, eligible patients will be randomly assigned to a verum acupuncture (VA), sham acupuncture (SA), or waitlist control group in a 1:1:1 ratio and will receive an 8-week intervention or wait. Figure 1 shows the flow chart of this trial. This study will be conducted in accordance with the Declaration of Helsinki, the Consolidated Standards of Reporting Trials (CONSORT) guidelines (50), and the Revised Standards for Reporting Interventions in Clinical Trials of Acupuncture (STRICTA) guidelines (51). This protocol has been reviewed and approved by the Ethics Committees of the Affiliated Hospital of Chengdu University of Traditional Chinese Medicine and the Public Health Clinical Center of Chengdu and has been registered at ClinicalTrials.gov (NCT07357688).

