#### Outcomes

##### Primary outcome measure

The primary outcome is the change from baseline to week 8 in the SDMT score.

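### The printed means and SDs do not give 36 per group: unadjusted power at that size is about 46% for the three-group test and 19% for verum versus sham, not 80%.

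*Protocol article*

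**What the plan says.** The section Sample size calculation of the protocol article prints these inputs and the result:

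- Expected SDMT changes at week 8, as mean ± SD: "3.75 ± 4.95, 2.45 ± 5.21, and 1.30 ± 4.35 for the VA, SA, and waitlist control groups, respectively".
- Error rates and sidedness: "With *α* = 0.05, *β* = 0.2, a power of 0.8, and a two-sided test for group differences".
- Result, 36 evaluable participants per group: "a power of 0.8, and a two-sided test for group differences, 36 participants are required in each group".
- Inflation: "Assuming a 20% dropout rate, 43 cases are needed per group, resulting in a total sample size of 129 participants".

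The planning values are for the primary endpoint ("The primary outcome is the change from baseline to week 8 in the SDMT score"), and allocation is 1:1:1. The paragraph does not say which test or contrast was powered, and it gives no correlation or covariate R-squared. The section Statistical analysis plans an ANCOVA of the primary outcome with age, estimated premorbid intelligence and physical activity as covariates.

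**The concern.** The three means lie close together relative to their SDs. The largest gap, verum minus waitlist, is 2.45 points, about half an SD. The verum-sham gap is 1.30 points, about a quarter of an SD. Effects of that size normally need many more than 36 per group.

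If the stated power is wrong, the trial claims a property that it lacks. The Discussion says that the sham arm is there to isolate the specific effect of acupuncture. A reader who is told that power is 80% could take a non-significant verum-sham result as evidence against such an effect. On the plan's own assumptions, the trial would miss that effect about four times in five.

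**Working it through.** **Inputs** (all from Sample size calculation; 1:1:1 allocation from Study design). Means 3.75, 2.45, 1.30; SDs 4.95, 5.21, 4.35; two-sided α = 0.05; target power 0.80; stated n = 36 per group, 43 after dropout.

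**1. Trying to reproduce 36 with the three-group test.**

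- Grand mean = (3.75 + 2.45 + 1.30)/3 = 2.50. The deviations are 1.25, −0.05 and −1.20, and their sum of squares is 1.5625 + 0.0025 + 1.4400 = 3.005.
- Pooled SD = √[(24.5025 + 27.1441 + 18.9225)/3] = √23.523 = 4.850.
- f = √(3.005/3)/4.850 = 0.206.
- Noncentrality at n = 36: λ = 36 × 3.005/23.523 = 4.60, with 2 and 105 degrees of freedom and critical F = 3.08. Noncentral F power is **45.8%**. A simulation with the three unequal SDs gave 46.3%.
- Power is 79.8% at n = 76 and 80.3% at n = 77, so **77 per group** are needed.
- Replacing the pooled SD by the smallest of the three (4.35) gives 55% at n = 36; the largest (5.21) gives 40%.

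**2. Trying to reproduce 36 with a pairwise test.** SE = √[(SD₁² + SD₂²)/n], noncentrality δ = difference/SE, two-sided t test with 2(n − 1) degrees of freedom.

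| Comparison | Difference | SE at n = 36 | δ | Power at 36 | n per group for 80% |
|---|---|---|---|---|---|
| Verum vs sham | 1.30 | 1.198 | 1.085 | 18.8% | 241 |
| Verum vs waitlist | 2.45 | 1.098 | 2.231 | 59.5% | 58 |
| Sham vs waitlist | 1.15 | 1.131 | 1.017 | 17.1% | 275 |

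**3. Other readings.** Bonferroni correction only raises n. Verum against the mean of the two controls needs 82 per group two-sided, and both needling arms against waitlist need 78. The smallest n from any variant tried was 45 to 46, for a one-sided verum-waitlist test, which the stated two-sided test rules out.

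**4. What would give 36.** For the three-group test, 80% power at n = 36 needs an SD of about 3.30, which corresponds to a covariate R-squared of 1 − (3.30/4.85)² ≈ 0.54. For the pairwise tests, the R-squared needed is about 0.38 (verum vs waitlist) or 0.85 (verum vs sham).

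**5. Power at other group sizes.** A 20% loss from 43 leaves 43 × 0.8 = 34.4, about 34 evaluable per group.

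| Evaluable per group | Three-group F | Verum vs sham | Verum vs waitlist | Sham vs waitlist |
|---|---|---|---|---|
| 34 | 43% | 18% | 57% | 16% |
| 36 | 46% | 19% | 59% | 17% |
| 43 (no loss) | 53% | 22% | 67% | 20% |

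**6. Detectable difference.** At 36 per group with SD 4.85, 80% power requires δ = 2.841, so the detectable pairwise difference is 2.841 × 4.85 × √(2/36) = 3.25 points. The plan assumes 1.30 for verum-sham and 2.45 for verum-waitlist.

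**The case against.** The strongest reply is that the planned analysis is an ANCOVA, while the figures above are for unadjusted tests. The article condenses a fuller protocol, and a covariate setting may have been entered in the sample size software and recorded elsewhere. The powered contrast is not named, so verum versus sham need not be the one intended. If it was verum versus waitlist, an R-squared of about 0.38 would be enough.

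Part of this stands. The percentages must be labelled as unadjusted, and the 54% of variance explained applies to the three-group test only. Low verum-sham power follows from the same defect and is not a second arithmetic error. The abstract also promises only preliminary evidence.

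It does not rescue the figure. The article prints what reads as a complete set of inputs and a result that does not follow from them. The SDs already refer to change scores, and baseline SDMT is not among the listed covariates. Age, premorbid intelligence and physical activity would therefore have to explain between 38% and 85% of the variance in change, depending on the contrast, and no such assumption is stated. If an unstated input produced 36, the paragraph is still wrong as printed.

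**Conclusion.** The concern holds. No unadjusted two-sided test on the stated means and SDs yields 36 per group. Against a claimed 80%, power at 36 is 46% for the three-group test and 59% for the most favourable pair; for verum versus sham it is 19%. With the plan's own dropout applied to 43, the corresponding figures fall to 43%, 57% and 18%. The three-group test would need 77 evaluable per group, or 231 in total, against 3 × 36 = 108 planned.

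These results assume that the printed means and SDs are the planning values, that changes are roughly normal, and that covariates contribute nothing. Covariates would raise power, but by an amount that the document gives no basis for estimating.

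**What to change.** Rewrite the power statement in Sample size calculation:

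- Name the test and contrast to which the power statement refers.
- If 129 is kept, replace the 80% claim with figures that reproduce, labelled as unadjusted: about 46% (three-group), 19% (verum vs sham) and 59% (verum vs waitlist) at 36 evaluable per group, or 43%, 18% and 57% at the 34 expected after 20% loss. Give the detectable pairwise difference of about 3.25 points at 36 per group.
- If a covariate R-squared entered the software calculation, state its value and source so that 36 can be reproduced.
- Add that a non-significant verum-sham difference cannot be read as no specific effect, and that the estimate will be reported with its confidence interval.

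The cost is one rewritten paragraph and a less favourable stated power; no extra patients are needed. Enlarging the trial is the alternative if 80% power is to be kept as a claim, at 77 evaluable per group for the three-group test and more for verum versus sham.

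### The 20% dropout allowance falls short: 43 randomised per group leaves about 34 completers, not the 36 the plan requires

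*Protocol article*

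**What the plan says.** The Sample size calculation section of the protocol article makes three linked statements. It takes expected SDMT changes at week 8 of "3.75 ± 4.95, 2.45 ± 5.21, and 1.30 ± 4.35 for the VA, SA, and waitlist control groups". From these, with α = 0.05 and "a power of 0.8, and a two-sided test for group differences", it concludes that "36 participants are required in each group". It then adds the allowance for loss: "Assuming a 20% dropout rate, 43 cases are needed per group, resulting in a total sample size of 129 participants".

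Allocation is 1:1:1 (Study design), so the total is three times the group figure, and 3 × 43 = 129 is consistent. The Statistical analysis section specifies an intention-to-treat analysis of everyone randomised and adds: "The missing value will be handled using multiple imputations".

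**The concern.** A dropout allowance has one purpose: after the assumed fraction has been lost, the required number must remain. Increasing the requirement by 20% does not achieve this, because the 20% loss then applies to the larger randomised number. Here 20% of 43 is 8.6, whereas the allowance adds only 7.

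The stated trial size therefore does not deliver the number of evaluable patients it promises at the dropout rate it assumes. Readers will take 129 as sized to retain the stated power at 20% dropout, and on the article's own figures it is not. The total of 129 is repeated in the Abstract and in Study design.

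**Working it through.** **Inputs**, all from the Sample size calculation section: 36 required per group; 20% dropout; 43 per group and 129 in total after the allowance; mean changes 3.75, 2.45 and 1.30; SDs 4.95, 5.21 and 4.35.

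**1. Reproducing the printed figure.** The article gives no inflation formula. Two forms are in common use:

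| Form | Per group | Total |
|---|---|---|
| n × (1 + d) = 36 × 1.2 | 43.2: 43 rounded down, 44 rounded up | 129 or 132 |
| n / (1 − d) = 36 / 0.80 | 45 | 135 |

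Of these, only the first, rounded down, gives 43. That this form was used is an inference.

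**2. Does 43 do the job?**

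- Expected completers per group: 43 × 0.80 = 34.4, against 36.
- Expected completers in total: 129 × 0.80 = 103.2, against 3 × 36 = 108.
- Largest dropout rate that still leaves 36: (43 − 36)/43 = 7/43 = 16.3%.
- With 45 per group: 45 × 0.80 = 36 exactly.

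This step uses only the printed 36, 20% and 43, so it does not depend on the inference in step 1.

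**3. Chance of reaching 36.** Assume each participant drops out independently with probability 0.20. The probability that a group of 43 keeps at least 36 is 0.35 (binomial), and that all three groups do is 0.35³ ≈ 0.04. For a group of 45 the first figure is 0.59.

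**4. Cost in power, taking 36 as correct.** Suppose 36 per group gave exactly 80% power at two-sided α = 0.05.

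- Three-group F test: the non-centrality parameter scales with n, so at 34 it is 34/36 of its value at 36. Power is 77.5% at 34 and 78.0% at 34.4.
- Two-group comparison (normal approximation): the standardised difference falls from 1.960 + 0.842 = 2.802 to 2.802 × √(34/36) = 2.723. Power is Φ(2.723 − 1.960) = 77.7%.

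The dropout step therefore costs about 2 to 2.5 points.

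**5. Cost in power on the stated means and SDs.** The pooled SD is √[(4.95² + 5.21² + 4.35²)/3] = 4.85. The grand mean is 2.50, and the sum of squared deviations of the means is 1.25² + 0.05² + 1.20² = 3.005. The non-centrality parameter is n × 3.005/4.85². For VA against waitlist, the difference is 2.45 and the SD is √[(4.95² + 4.35²)/2] = 4.66.

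| Test (unadjusted, two-sided 5%) | n = 36 | n = 34 |
|---|---|---|
| Three-group F test | 45.8% | 43.5% |
| VA against waitlist, t test | 59.5% | 57.0% |

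The drop is again 2 to 2.5 points. The low level of both columns has another cause: 36 per group does not reproduce from the stated means and SDs (the three-group F test needs 77 per group for 80%). That is a separate problem and should not be attributed to the dropout step.

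**The case against.** The strongest case on the other side has four parts.

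*The difference is minor.* It amounts to 1.6 expected completers per group, or two more randomised per group, and the 20% is itself a round assumption. Under the simple randomisation specified in Randomization and blinding, the size of any one arm has an SD of √(129 × 1/3 × 2/3) = 5.4, which exceeds the two patients in question. All of this is true, and it limits how much weight the point deserves. It does not make the sentence correct.

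*Everyone randomised is analysed, with multiple imputation.* Dropouts are not simply removed, but the plan itself treats dropout as lost information, since otherwise 36 would need no inflation. Imputation does not restore week-8 scores that were never observed. If dropout cost no information, 36 would be enough; if it costs the full 20%, 45 are needed. Neither reading gives 43.

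*The formula is inferred.* This stands, and the multiplication by 1.2 should be described as the likely explanation only. The shortfall holds without it.

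*The base figure is the larger problem.* This also stands. With 45 completers per group, the unadjusted three-group test on the stated means would have only 55% power, so repairing the allowance alone would not secure 80%. The planned ANCOVA could raise power, but the article states no covariate–outcome correlation. These points argue for correcting both steps together. They do not excuse the allowance, and the same shortcut would under-inflate any corrected base figure.

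**Conclusion.** The concern holds. On the article's own figures, 43 per group does not leave 36 after 20% dropout: it leaves about 34 (103 in total against 108), and it covers dropout only up to 16.3%. The number that matches the claim is 45 per group, six more patients in total than planned.

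The conclusion rests on the usual meaning of a dropout rate, the fraction of those randomised who are lost, and on reading 36 as the number that must remain. It does not depend on whether 36 is itself right. The consequence is modest, about 2 to 2.5 points of power, and no outcome, comparison or analysis method is affected. It is an arithmetic error in the sample size justification that should be corrected.

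**What to change.** Keep 129 and restate the sentence in one of two ways:

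- 43 per group retains 36 completers if dropout does not exceed about 16%; or
- at 20% dropout about 34 completers per group are expected, with power quoted for 34.

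If the claim of 36 completers at 20% dropout is to remain, print 45 per group and 135 in total, and change the total wherever it appears.

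Either restatement costs one sentence and a slightly less favourable figure, with no extra patients. The alternative costs six more patients. Whichever is chosen, recheck the base figure of 36 in the same revision, and apply division by (1 − dropout rate), rounded up, to whatever base figure results.
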